# Withdrawal of Subjects*

14. 1 Describe anticipated circumstances under which subjects will be withdrawn from the research without their consent.

Participation is voluntary, and can be terminated at any time by participants. This study has minimal risk to patients, so unexpected withdrawal due to safety reasons from the study design is not expected to occur.

14.2 Describe any procedures for orderly termination.

The request for termination will be managed and documented by the study coordinator. Study personnel, study and treating therapists will be notified.

14.3 Describe procedures that will be followed when subjects withdraw from the research, including partial withdrawal from procedures with continued data collection.

The study coordinator will be made aware of the withdrawal and coordinate this. The coordinator will coordinate the return of study equipment by the family. We will retain study data related to the subject collected prior to the subject's withdrawal from the study. Study-related events scheduled after the withdrawal date will be cancelled and no further data collected.

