# Study Endpoints

- 1. Describe the primary and secondary study endpoints.

The primary study endpoints acquiring the primary study outcomes of standardized behavioral measures of speech, language, and literacy outcomes. These include Raw Score, Standard Score, Percentile Rank, Age Equivalent, and Growth Scale Values where applicable for the following tests: Receptive One Word Picture Vocabulary Test, Clinical Evaluation of Language Fundamentals Preschool-3 and subtests). The clinical standard test-retest interval for these behavioral measures in D/HH children is 6 months.

Secondary outcomes include measures of the impact on therapy experience, book engagement/book-reading habits, and feedback on the design and usability of the Hear Me Read app. These will be measured with parent/caregiver and SLP questionnaires, and in-app metrics of app usage.

Primary outcomes are measured pre-trial, at 6 months (after 1st intervention arm), and at 12 months (after 2nd intervention arm). Secondary outcomes are measured at 6 months (after 1st intervention arm), and at 12 months (after 2nd intervention arm). Study phase will end upon cessation of data collection after the 2nd intervention arm and participants’ participation.

The secondary endpoint will be the completion of data analysis, which concludes the management of PHI.

- 1. Describe any primary or secondary safety endpoints.

N/A, as this study poses no more than minimal risk to patients enrolled.

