- Children are then continued in the next phase of the study (**Intervention Period 2)** with the **SLT+Digital intervention** **for 6 months**. In the SLT+Digital phase, the child will receive in-person therapy in identical fashion as the SLT-only intervention period with a SLP_T,_ and also with the same prescribed reading time. However, the SLP_T_ will now **additionally** assign storybooks through HMR. Difficulties using HMR will be directed to Research Information Solutions and Innovation (RISI) at The Research Institute at NCH who is budgeted for support, along with study coordinator. Contact information will be in the **Hear Me Read Training document.**
- At the conclusion of **Intervention Period 2 (Post-SLT+Digital SLP Evaluation)**, a final assessment battery is completed by the SLP_T_ as part of standard clinical care. Scores on the ROWPVT-4 and the CELF-P3 will be collected in the **Therapist - Data collection Form**, built in REDCap.
- SLP_T_ will record evaluations on an NCH device connected to NCH’s secured network. Once recorded, video files will be stored on a secured encrypted NCH drive, accessible only to study team members and the SLP_T_. Once the video is uploaded to the NCH server, it will be deleted from the device.
- To minimize bias, SLP_S_ will be unaware if the re-evaluation is Post-SLT-only or Post-SLT+Digital, whenever possible.
- As before, a survey (**Post-SLT+Digital -Parent/Caregiver**) on the therapy experience will be filled out by the parent/caregiver after the intervention period.
- Parents/caregivers will additionally fill out **Hear Me Read Feedback-Parent/Caregiver** and questionnaires to provide user feedback on the digital platform.

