**Study documents below.**

**Data Source Forms (electronic in REDCap, input from iPad or abstracted from EPIC):**

- Therapist - Data Collection Form (All part of standard clinical care):
  - Pre-Trial SLP Evaluation data (ROWPVT-4, CELF-P3)
  - Post-SLT-only SLP Evaluation data (ROWPVT-4, CELF-P3)
  - Post-SLT+Digital SLP Evaluation data (ROWPVT-4, CELF-P3)
- Participating parent/caregiver and treating therapist surveys:
  - Pre-Trial Parent/Caregiver Survey
  - Post-SLT-only – Parent/Caregiver
  - Post-SLT+Digital – Parent/Caregiver
  - Hear Me Read Feedback – Parent/Caregiver
  - Post-SLT-only – Treating Therapist
  - Post-SLT+Digital – Treating Therapist
  - Hear Me Read Feedback – Treating Therapist
  - Reading Questionnaires (Parent/Caregiver)

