# Data Management* and Confidentiality

17.1 Describe the data analysis plan, including any statistical procedures or power analysis.

Raw Score, Standard Score, Percentile Rank, Age Equivalent, and Growth Scale Values for the assessment tests will be measured. Power analysis was based off of Raw Score. A 2-by-2 repeated measures design consists of two groups of subjects, each measured at two time points. In this case, the primary goal of the study is to compare the change across time in group 1 to the change across time in group 2. Sample sizes of 13 in group 1 and 13 in group 2 achieve 92% power to detect a difference in mean changes of 2.0 with a standard deviation of 1.0 at the first time point, a standard deviation of 1.0 at the second time point, and a correlation between measurement pairs of 0.300. The significance level (alpha) is 0.010 using a two-sided, two-sample t-test. To detect a mean 1.5 point difference (all else being equal), we would need **21 patients in each group**. To detect a mean 1 point difference (all else being equal), we calculate we would need 44 patients in each arm.

We plan to analyze Intervention Period 1 (SLT) and Intervention Period 2 (SLT+Digital) together using mixed-effects models to account for differences between interventions 1 and 2. For the primary outcomes, evaluate baseline assessments and compare values between groups using Pearson chi-square tests, t-tests, and Wilcoxon-Mann-Whitney tests. If any imbalance in patient characteristics (e.g. age, frequency of therapy) is detected between groups, the imbalanced characteristics will be adjusted for in multivariable mixed-effects linear regression analyses.

All statistical analyses will be conducted using SAS Enterprise Guide, version 7.15 (SAS Institute Inc). Outcomes are reported for the intention-to-treat population and the also reported for the per protocol population. A 2-sided P < .05 was considered statistically significant.

17.2 Describe the steps that will be taken to secure the data (e.g., training, authorization of access, password protection, encryption, physical controls, certificates of confidentiality, and separation of identifiers and data) during storage, use, and transmission.

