**Child and Parent/Caregiver Participants:**

We will follow SOP: Written Documentation of Consent (HRP-091).

Potential subjects will be approached at a NCH site or via phone or email after identification and referral to study staff. Study personnel (not the PI) will discuss the study and review the consent form (in person, virtually, or over the phone) with the legal guardian or legally authorized representative. Please refer to the attached document: **Informed Consent** **Form.**

The written form and study information will inform potential participants about the details of the study and written in plain language at a level that reflects the reading ability of potential participants. The informed consent document will be reviewed and signed electronically, via REDCap. A copy will be emailed to the participant. The informed consent process may take place at NCH, virtually through a NCH-approved videoconferencing platform or via phone. A copy of **Informed Consent** **Form** will be provided to families as part of their study packet. Information about the study and researchers, including contact information, will be provided in case the family wishes to review documents on their own time and pace and notify the study staff of participation.

This study does not adversely affect the rights and welfare of subjects, and does not involve more than minimal risk.

If at any of the therapy visits, parents indicate they wish to withdraw from the study or consent, they may do so without retaliation.

No assent will be obtained from the children in this study, as all children will be under age 7 during the study period.

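### Section 14.3 offers withdrawing families only a route that ends all data collection, so routine-care 12-month scores, the only measurement after HMR, are lost to the intention-to-treat analysis

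*Protocol*

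**What the plan says.** The form's prompt in protocol section 14.3 (Withdrawal of Subjects) asks for the procedures on withdrawal, "including partial withdrawal from procedures with continued data collection". The answer describes one path. The coordinator arranges return of the equipment. Earlier data are kept ("We will retain study data related to the subject collected prior to" the withdrawal). After that, "Study-related events scheduled after the withdrawal date will be cancelled and no further data collected". No route is described for a family that gives up the app or the surveys but would let its chart scores be used.

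The Consent Process section refers to visits at which "parents indicate they wish to withdraw from the study or consent", and it too draws no line between leaving procedures and withdrawing permission to use data.

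On the outcome data, the Study Endpoints section states: "Primary outcomes are measured pre-trial, at 6 months (after 1st intervention arm), and at 12 months (after 2nd intervention arm"). Procedures Involved says of the end of Intervention Period 2 that "a final assessment battery is completed by the SLP_T_ as part of standard clinical care". The list of source forms in section 6.4 describes the form holding all three score sets as "Therapist - Data Collection Form (All part of standard clinical care"), and allows source forms to be filled from the electronic medical record.

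On analysis, section 17.1 plans mixed-effects models over both periods together and adds: "Outcomes are reported for the intention-to-treat population and the also reported for the per protocol population".

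**The concern.** Every child has SLT-only first and SLT+Digital second, so HMR is reflected only in the change from 6 to 12 months. A child whose 12-month score is not collected has no observed Period 2 change, and no concurrent arm has comparable losses to set against it.

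Reasons for leaving during Period 2 could well relate to the app. The protocol's Background raises distraction and reduced face-to-face interaction with digital books, and its Risks section raises screen time and time spent troubleshooting. If families whose children respond poorly are likelier to withdraw, the missing scores are related to the effect being estimated.

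The scores being given up need no study visit and will often sit in the chart anyway. An SAP cannot repair this, because it cannot analyse scores that the protocol says will not be collected.

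**Working it through.** **1. The plan's own figure.** Section 12.1 gives n = 43, 90% power, mean paired difference 0.75, SD 1.0, two-sided alpha 0.001, paired t-test. With the noncentral t distribution (df = n − 1, noncentrality = 0.75 × √n / 1.0), the smallest n with at least 90% power is 43, with power 90.4%. The stated figure reproduces. Planned enrolment is 50. The margin is 50 − 43 = 7 children, or 7/50 = 14%. The protocol does not call this a dropout allowance and states no dropout rate.

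**2. Is this mainly a power problem?** Power of the paired test by number of complete pairs (losses from 50 are assumed):

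| Pairs | Loss | Power, alpha 0.001 |
|---|---|---|
| 50 | 0% | 95.7% |
| 45 | 10% | 92.3% |
| 43 | 14% | 90.4% |
| 40 | 20% | 86.9% |
| 35 | 30% | 78.6% |

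At the 0.05 level that section 17.1 uses for analysis, power is still 99.1% with 35 pairs. Power is secondary; the question is bias.

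**3. Simple illustration of bias.** Assume that completers average 0.75, that withdrawn children have a true paired difference of 0, and that the estimate is the unadjusted completers' mean.

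Mean over all enrolled = (1 − w) × 0.75 + w × 0, where w is the fraction withdrawn.

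- w = 10%: 0.675
- w = 14%: (43 × 0.75 + 7 × 0)/50 = 0.645, so the completers' 0.75 is 0.75/0.645 = 1.16 times the all-children value
- w = 20%: 0.600
- w = 30%: 0.525

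Both w and the zero gain are assumptions.

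**4. Does the planned model remove the problem?** This was simulated with 50 children, three visits and 4,000 repetitions. Visit means were 0, 1 and 2.75, so the true difference in gains over all children is 1.75 − 1 = 0.75. The child-level SD was 1 and the visit error SD was 1/√6, which makes the SD of the paired difference 1.0. About 22% withdrew after the 6-month score, with lower gain making withdrawal likelier. A completers' mean was compared with a likelihood estimate using all retained scores.

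| Withdrawal depends on | Completers' mean | Likelihood, all retained scores | Truth |
|---|---|---|---|
| Observed Period 1 gain | 0.57 | 0.75 | 0.75 |
| Unseen Period 2 gain | 0.93 | 0.84 | 0.75 |

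In the first case the retained scores and the model remove the bias, which for completers was downward. In the second they halve it, from 0.18 to 0.09, and leave the rest. The lost 12-month scores are what would be needed to remove the remainder.

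**The case against.** A reader might infer that the rule turns the intention-to-treat report into a completers-only analysis. The documents do not support that. Section 14.3 keeps scores from before withdrawal, and the mixed-effects models in section 17.1 can use them. Only the paired contrast used for sizing in section 12.1 needs all three scores.

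A reader might also infer that any family that dislikes or stops using the app loses its 12-month scores. No text says so. The trigger is withdrawal from the research, the study or consent, and return of the iPad follows withdrawal rather than causing it. A non-user who stays enrolled still has the final battery. For the same reason, it does not follow that the intention-to-treat and per-protocol results would largely coincide.

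Other objections also stand:

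- Families may leave at any time, so some losses fall in Period 1 and cannot reflect how HMR was received.
- The direction of bias depends on who leaves.
- Ending collection when a family withdraws permission altogether is proper.
- Routine scores are not assured. Section 13.1 allows treating SLPs from outside the hospital; in 2019 only 141 of 411 children in the age range had a speech-language evaluation; and section 16.1 hopes that the study itself will reduce loss to follow-up.
- Scores taken only from the chart may lack the study SLP's validation.

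These points limit the size of the concern and what the remedy can recover. They do not remove the fact that section 14.3 answers a question about partial withdrawal with a rule that ends all collection.

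**Conclusion.** The point holds in a limited form. The withdrawal rule gives up routine-care outcome scores that will often exist, including the only scores after HMR, while the protocol promises an intention-to-treat report. The planned model protects that report if data are missing at random. If withdrawal depends on the unseen response to HMR, the estimate may be biased, plausibly upward.

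The size cannot be derived from the protocol. The 0.645 against 0.75 rests on an assumed 7 withdrawals with zero gain and an unadjusted completers' mean. The 0.84 against a true 0.75 rests on an assumed 22% withdrawal driven by Period 2 gain. Neither is an estimate for this trial. The change is worth making because it is cheap and because scores left uncollected under the current rule cannot be restored by analysis.

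**What to change.** In section 14.3, and in the consent form if it does not already do so (it was not available for this review), separate two situations:

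- **(a) Stopping HMR, surveys or study procedures.** State that stopping the app alone is not withdrawal. With the family's permission, keep abstracting the routine 6- and 12-month ROWPVT-4 and CELF-P3 scores where available, and include them in the intention-to-treat analysis.
- **(b) Withdrawing permission to use records.** Stop all collection from that date and keep what was collected before, as now.

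Record which of the two applies, and when, for each family. Flag scores that lack the study SLP's validation.

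The cost is protocol wording, consent wording if needed, and an IRB amendment. No visits are added, since the evaluations are described as standard care. Some scores will still be missing, because of external SLPs or missed routine evaluations, so the missing-at-random assumption will still need examining.

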# Risks to Subjects*

15.1 List the reasonably foreseeable risks, discomforts, hazards, or inconveniences to the subjects related the subjects’ participation in the research. Include as may be useful for the IRB’s consideration, a description of the probability, magnitude, duration, and reversibility of the risks. Consider physical, psychological, social, legal, and economic risks.

Participants can choose to not participate, and this will have no consequences to clinical care or employment.

The duration of time spent using screens/digital devices is important to consider. The prescribed reading time using the HMR app is not in excess of recommendations made by the American Academy of Pediatrics, and we are not enrolling children aged 2 or younger (who are at greatest risk). To encourage healthy overall screen use, our study packet will include the following screen safety information:

- - American Academy of Pediatrics information: AAP - Tips for Parents in the Digital Age and Media Use Plan
    - [Children and Media - Tips for Parents​](https://www.healthychildren.org/English/family-life/Media/Pages/Tips-for-Parents-Digital-Age.aspx):
      - <https://www.healthychildren.org/English/family-life/Media/Pages/Tips-for-Parents-Digital-Age.aspx>
    - Making a Media Use Plan:
      - [www.HealthyChildren.org/MediaUsePlan](http://www.healthychildren.org/MediaUsePlan)

Economic risks are not expected to be excessive, given that interventions will take place during standard clinical care visits. No additional parking or transportation needs are expected. Time spent learning and troubleshooting the software could occur. We will provide contact information to the Research Information Solutions and Innovation (RISI) at The Research Institute at Nationwide Children's Hospital, who is budgeted to provide ongoing support for this purpose.

Although we will take every precaution, there is a small chance of loss of confidential study information. The study staff, and Nationwide Children’s Hospital technology teams, have taken precautions to ensure all the information, including videos, collected on the iPad are stored and transferred securely.

15.2 If applicable, indicate which procedures may have risks to the subjects that are currently unforeseeable.

**N/A** – no more than Minimal Risk to subjects

15.3 If applicable, indicate which procedures may have risks to an embryo or fetus should the subject be or become pregnant.

**N/A**

15.4 If applicable, describe risks to others who are not subjects.

**N/A**

# Potential Benefits to Subjects*

16.1 Describe the potential benefits that individual subjects may experience from taking part in the research. Include as may be useful for the IRB’s consideration, the probability, magnitude, and duration of the potential benefits.

At this time, little is known about digital reading interventions in young D/HH children. Potentially, structured prospective follow up with children in this study could decrease the loss to follow up and improve compliance with speech-language therapy that is prescribed. Increased reading and book engagement may occur, and this generally provides educational and developmental benefits in all children, including those that are D/HH.

16.2 Indicate if there is no direct benefit. Do not include benefits to society or others.

There may be no direct benefit.

# Data Management* and Confidentiality

17.1 Describe the data analysis plan, including any statistical procedures or power analysis.

Raw Score, Standard Score, Percentile Rank, Age Equivalent, and Growth Scale Values for the assessment tests will be measured. Power analysis was based off of Raw Score. A 2-by-2 repeated measures design consists of two groups of subjects, each measured at two time points. In this case, the primary goal of the study is to compare the change across time in group 1 to the change across time in group 2. Sample sizes of 13 in group 1 and 13 in group 2 achieve 92% power to detect a difference in mean changes of 2.0 with a standard deviation of 1.0 at the first time point, a standard deviation of 1.0 at the second time point, and a correlation between measurement pairs of 0.300. The significance level (alpha) is 0.010 using a two-sided, two-sample t-test. To detect a mean 1.5 point difference (all else being equal), we would need **21 patients in each group**. To detect a mean 1 point difference (all else being equal), we calculate we would need 44 patients in each arm.

We plan to analyze Intervention Period 1 (SLT) and Intervention Period 2 (SLT+Digital) together using mixed-effects models to account for differences between interventions 1 and 2. For the primary outcomes, evaluate baseline assessments and compare values between groups using Pearson chi-square tests, t-tests, and Wilcoxon-Mann-Whitney tests. If any imbalance in patient characteristics (e.g. age, frequency of therapy) is detected between groups, the imbalanced characteristics will be adjusted for in multivariable mixed-effects linear regression analyses.

All statistical analyses will be conducted using SAS Enterprise Guide, version 7.15 (SAS Institute Inc). Outcomes are reported for the intention-to-treat population and the also reported for the per protocol population. A 2-sided P < .05 was considered statistically significant.

17.2 Describe the steps that will be taken to secure the data (e.g., training, authorization of access, password protection, encryption, physical controls, certificates of confidentiality, and separation of identifiers and data) during storage, use, and transmission.

Privacy and security will be maintained by minimizing the amount of identifiable data as much as possible. All demographic, clinical, and outcome data will be recorded by local study staff in the study’s central REDCap database maintained at NCH. REDCap is a network software suite that provides data storage, encryption, and password protection for health information, to which only study staff will have access. Any collected paper information will be entered and compiled in an Excel or REDCap database (or password protected computer files). Paper copies will be stored in locked study cabinets until entry, and then shredded in appropriate, in secure NCH bins after electronic capture. Files and video/audio recorded materials will be maintained on computers located at NCH that are maintained on a secure network. Only approved research personnel will be given access to identifiable participant information. All necessary identifiers will be used only to identify the relevant source documents. At the conclusion of data collection, a unique identifier will be assigned to each participant and the identifiers will be deleted from the primary dataset and stored in a separate list. A list linking the assigned code number to the individual subject will be maintained separately from the other research data.

NCH study iPads will be provided to intervention study patients directly, at first therapy visit when HMR intervention is initiated. Hear Me Read will be used as prescribed by a treating speech-language therapist. The iPads provided to study patients that have Hear Me Read software will be NCH study iPads, managed and supported by Research Information Solutions and Innovation (RISI) at The Research Institute at Nationwide Children's Hospital. Serial numbers of the iPads will be documented and stored. These iPads will be password protected, requiring input password before access to any apps. Passwords will be provided only to therapists, study staff, investigators, and to the study family. Upon completion of the study, investigators will store the iPads in a locked drawer, in a locked office at NCH. When data is accessed from the iPads and stored on a secure server on the NCH network, the data will be deleted from the iPads. In-app metrics will be taken from the iPads upon return of the devices, minimizing transfers of information regarding use of the app to a single event. This transfer would be done on secure NCH servers and networks by RISI staff.

The data set will be maintained for 6 years after the study closure.

Data, including audio and video data, will not be stored for future research, unless written permission doing so is voluntarily granted during the informed consent process.

17.3 Describe any procedures that will be used for quality control of collected data.

A trained speech-language pathologist will validate the post-intervention assessment battery of tests (vocabulary, speech, language, literacy outcome measures) for all of the study patients, ensuring consistent data collection. This SLP_s_ is not involved in the treatment of patients and is trained and familiar with the outcome measures since they are used as part of clinical practice.

A study coordinator will ensure that organization and execution of the study follows the protocol, and the surveys/questionnaires are administered.

17.4 Describe how data or specimens will be handled study-wide:

**N/A** – this is a single site study

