# Local Number of Subjects

12.1 Indicate the total number of subjects to be accrued locally.

A **power analysis** was performed, based off of Raw Scores with the following rationale: A repeated measures design will evaluate the effect of the intervention within person. In this case, the primary goal of the study is to compare the change across time during SLT therapy alone to the change across time with SLT + Digital. A sample size of 43 achieves 90% power to detect a mean of paired differences of 0.75 with an estimated standard deviation of 1.0 and with a significance level of 0.001 using a two-sided paired t-test.   We plan to enroll 50 children at NCH, as well as a parent/caregiver for each child and the child’s treating SLP.

12.2 If applicable, distinguish between the number of subjects who are expected to be enrolled and screened, and the number of subjects needed to complete the research procedures (i.e., numbers of subjects excluding screen failures.)

We expect approximately 411 unique D/HH children in the age range to be seen by our Hearing Program in 1 year, based on 2019 data. Of these, 141 completed a speech and language evaluation in that year and 270 did not. With prospective attention to scheduling and these volumes, we anticipate screening approximately 250-300 patients to achieve 50 that would enroll.

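### Section 17.1 frames the primary comparison as two separate groups and a two-sample t-test, but the trial has one group; this contradicts Section 12.1 and overstates the power for the within-child contrast

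*Protocol*

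**What the plan says.** Section 17.1 (Data Management and Confidentiality) introduces its power calculation with "A 2-by-2 repeated measures design consists of two groups of subjects, each measured at two time points", and gives the study's primary goal as being to "compare the change across time in group 1 to the change across time in group 2". The calculation reads "Sample sizes of 13 in group 1 and 13 in group 2 achieve 92% power to detect a difference in mean changes of 2.0". Its other inputs are an SD of 1.0 for the scores at both visits and a within-pair correlation of 0.300. On the test it says: "The significance level (alpha) is 0.010 using a two-sided, two-sample t-test". It also gives 21 per group for a 1.5-point difference and 44 per arm for a 1-point difference.

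The next paragraph of 17.1 turns to the outcome analysis. The two intervention periods are to be analysed "together using mixed-effects models to account for differences between interventions 1 and 2". That paragraph still refers to baseline values compared between groups by unpaired tests, and sets two-sided significance at 0.05.

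Section 12.1 (Local Number of Subjects) describes the same goal as a within-person evaluation: 43 children, 90% power, mean paired difference 0.75, SD 1.0, "with a significance level of 0.001 using a two-sided paired t-test".

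Procedures Involved places every child in SLT-only first and SLT+Digital second. Study Endpoints says: "Primary outcomes are measured pre-trial, at 6 months (after 1st intervention arm), and at 12 months (after 2nd intervention arm".

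**The concern.** The trial has no second group and three scores per child, not four. Write Y0, Y6 and Y12 for the scores, D1 = Y6 − Y0 for the SLT-only change and D2 = Y12 − Y6 for the SLT+Digital change. D1 and D2 come from the same child, and Y6 enters them with opposite signs. Measurement error in Y6 therefore pushes the two changes apart, and the variance of D2 − D1 is not the sum of two independent variances, as a two-sample t-test assumes.

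Two things are at stake. The sample sizes in 17.1 rest on the wrong variance, so their stated power does not apply to this trial. And 17.1 is the data analysis section: if its two-group layout were followed when the mixed model is built, the standard error of the effect could be too small. The protocol would also contain two incompatible descriptions of its primary comparison.

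**Working it through.** **Inputs.** From 17.1: SD 1.0 at each time point, correlation 0.3 between measurement pairs, two-sided alpha 0.010, and n = 13, 21 and 44 for differences of 2.0, 1.5 and 1.0. From 12.1: n = 43, difference 0.75, SD 1.0, alpha 0.001, and planned enrolment of 50.

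**Assumption.** The correlation between the 0- and 12-month scores is not stated. I use 0.3 (all visits equally correlated) and 0.3² = 0.09 (first-order autoregressive).

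**Step 1: reproduce the plan's figures.** The SD of a change is √(1 + 1 − 2 × 0.3) = √1.4 = 1.183. Noncentral-t power for a two-sided two-sample t-test at alpha 0.01 is:

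- 13 per group, difference 2.0: 92.4% (stated: 92%)
- 21 per group, difference 1.5: 91.3%
- 44 per group, difference 1.0: 90.5%

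The values 21 and 44 are the smallest that reach 90%. Section 12.1 also reproduces: n = 43 gives 90.4%. Each calculation is arithmetically correct for the design it assumes.

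**Step 2: variance of the actual contrast.** D2 − D1 = Y12 − 2·Y6 + Y0.

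- Var(D1) = Var(D2) = 1.4.
- Cov(D1, D2) = corr(6,12) − 1 − corr(0,12) + corr(0,6) = 0.3 − 1 − corr(0,12) + 0.3.
- With corr(0,12) = 0.3, Cov = −0.70, the changes correlate −0.50, and Var(D2 − D1) = 2.8 + 1.4 = 4.20 (SD 2.05).
- With corr(0,12) = 0.09, Cov = −0.49, the changes correlate −0.35, and Var(D2 − D1) = 2.8 + 0.98 = 3.78 (SD 1.94).

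The two-sample formula assumes 2.8. The true variance is 4.20/2.8 = 1.50 or 3.78/2.8 = 1.35 times that.

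**Step 3: power for the within-child contrast.** Noncentral-t power of a paired test at alpha 0.01:

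| Children | Difference | Two-sample basis of 17.1 | corr(0,12) = 0.3 | corr(0,12) = 0.09 |
|---|---|---|---|---|
| 13 | 2.0 | 92.4% | 67% | 73% |
| 21 | 1.5 | 91.3% | 69% | 75% |
| 44 | 1.0 | 90.5% | 70% | 76% |

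For 92% paired power the numbers are 21 or 19 children (difference 2.0), 33 or 31 (1.5) and 70 or 64 (1.0), in the same column order. At the planned 50 children, a 1-point difference has 78% or 83%.

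**Step 4: false-positive rate if the two-group layout were used.** With variance ratio k, an independent-groups test rejects with probability 2·(1 − Φ(z/√k)).

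- k = 1.50: 11.0% at nominal 5%, 3.5% at nominal 1%.
- k = 1.35: 9.2% at nominal 5%, 2.7% at nominal 1%.

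Simulation at N = 50 agrees (9–11% and about 2.6–3.6%). The paired contrast stays at 5% and 1%.

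**Step 5: false-positive rate of a mixed model with three scores per child.** A child random intercept, each score entered once and contrast 1, −2, 1, simulated at N = 50, rejects 4.9% (equal correlation) or 3.1% (autoregressive) at nominal 5%. It is not inflated in either case.

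**Step 6: sensitivity to varying growth rates.** Starting from equal correlation, give children a random slope with variance s² per 6 months. The correlation of the two changes becomes (s² − 0.7)/(1.4 + s²). The independent-groups test then rejects 7.4% at s² = 0.35 and 5.0% at s² = 0.7 (slope SD 0.84), and falls below nominal for larger s².

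**The case against.** The strongest reply is that the two-sample t-test belongs to the power paragraph, while the outcome analysis is a mixed-effects model. The other t-tests in 17.1 sit in a sentence about baseline values and imbalance. A natural version of the stated model, with three scores per child, holds its error rate. Its random effects and covariance are the sort of detail a statistical analysis plan supplies, and 12.1 already states the within-person comparison.

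Most of this stands. A reader might infer from 17.1 that the effect will be tested as two independent groups, and so that the false-positive rate is two to three times nominal. The protocol does not say that. Nor does it say that the 6-month score is entered twice in a four-record model, which would be another route to inflation. The size of any inflation also depends on a correlation the protocol does not give, and it shrinks if growth rates vary.

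The reply does not rescue what 17.1 does state. The two-group description, the two-sample test and the sample sizes derived from them are on the page, do not fit a one-group trial and conflict with 12.1. Leaving model details to a later document does not correct a wrong statement in this one. Nor is the label mixed-effects a safeguard in itself: the only layout 17.1 describes is the wrong one.

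**Conclusion.** Section 17.1 misdescribes the primary comparison and contradicts 12.1. The established consequence concerns power: on 17.1's own inputs, its sample sizes give roughly 67–76% for the within-child contrast, against 92% stated at 13 and about 91% implied at 21 and 44. This rests on SD 1.0, correlation 0.3 between adjacent visits, alpha 0.01 and a 0-to-12-month correlation between 0.09 and 0.3.

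The sections also disagree on inputs. Those of 17.1 imply an SD of 1.94 to 2.05 for the paired difference, where 12.1 uses 1.0. Three significance levels appear: 0.001 in 12.1, and 0.010 and 0.05 in 17.1.

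Inflated type I error is a conditional risk, not a finding about the planned analysis.

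**What to change.** In 17.1:

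1. Delete the two-group, 2-by-2 description and the two-sample t-test.
2. State the primary comparison as the within-child contrast Y12 − 2·Y6 + Y0, estimated from a mixed model in which each visit score is entered once per child. With complete data and an unrestricted within-child covariance, this is the paired test of 12.1.
3. Restate the power figures for that contrast, or remove them, so that 12.1 and 17.1 give one test, one SD for the paired difference and one alpha. Give the assumed 0-to-12-month correlation if the SD is derived from visit-level inputs.

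The cost is wording only: no new data, visits or children are needed to correct the text. The price is a less favourable power statement if 17.1's inputs are kept.
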